### Data management

The questionnaires would be checked there and then by data editors who will edit data collection forms. Each data set will be edited twice. Any missing data would be communicated to the data collectors for rechecking. The data would be entered by two independent data entry operators separately in Epi data version 3.0. The data cleaning would be done by merging the two data and any discrepancy between the two records would be looked and corrected from the case report forms. The final (cleaned) data would be logically checked and transformed into SPSS version 21 for the analysis.

#### Statistical analysis

Mean (SD) would be used for quantitative variables and frequency and percentage for categorical variables. Recruitment, retention, and treatment fidelity will be reported as percentage. Student *t* test would be used to compare quantitative variables (change in physical activity, BP, BMI, and waist circumference before and after intervention) between groups. Chi-square test to compare qualitative variables like percent increase in fruits and vegetables between the 2 groups from baseline to follow-up. Analysis would be done on intention to treat basis, that is, all participants will be analyzed in the same group as at time of allocation.

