**Conclusion:**

SHEPP is a unique health education program for children as it focuses on children while involving the parents and teachers in the behavior change process. If found feasible and demonstrating potential efficacy on physical activity, dietary behaviors, and cardiometabolic parameters, we will be able to replicate this on a larger scale in public sector schools also.

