## Sample size

Since this is a parallel-group feasibility intervention trial in a school setting, where interventions can only be done on class level (in a group) and not individually due to ethical and administrative reasons, we included 12 classes of children from the intervention school and 12 from control school. Each class has approximately 40-45 students making a total sample size of approximately 540 participants in intervention and 540 in the control arm. This sample size is sufficient to measure feasibility outcomes of 70% recruitment, retention, and treatment fidelity. As mentioned by Thabane et al., for an expected completion rate (recruitment, retention, and treatment fidelity for this study) of 75%, the minimum required sample for the pilot study would be at least 75 participants using a 95% CI for the proportion and a margin of error (ME) of 0.05, a lower bound of this CI of 0.70 [35]. Hence, the abovementioned sample size for this study is sufficient to assess the feasibility outcomes.

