## Assignment of interventions

This is a non-randomized study. One school is allocated to SHEPP intervention after baseline data collection while the other school will carry on routine activity and will be subjected to intervention after follow-up data collection. The decision of selection of school for intervention therefore was based on convenience and was not randomized. The data collectors who will collect data will be blinded to the assignment of intervention. The physical activity trainer will conduct sessions in the intervention school and will have no role during the data collection.

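### The between-arm tests on the secondary outcomes treat children as independent, although SHEPP is delivered by class and each arm is a single school, so standard errors and p-values are too small and the contrast is one between two schools

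*Protocol article*

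**What the plan says.** The Statistical analysis section of the protocol article fixes the between-arm methods. For quantitative outcomes, a Student t test "would be used to compare quantitative variables (change in physical activity, BP, BMI, and waist circumference before and after intervention) between groups". For diet, "Chi-square test to compare qualitative variables like percent increase in fruits and vegetables between the 2 groups from baseline to follow-up". The analysis is by intention to treat: "all participants will be analyzed in the same group as at time of allocation". The section contains no class or school term, no adjustment for clustering, and no statement that the comparisons are descriptive only.

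The design is described elsewhere. Under Sample size, "interventions can only be done on class level (in a group) and not individually", with 12 classes of about 40 to 45 children in each school. Under Assignment of interventions, "One school is allocated to SHEPP intervention after baseline data collection while the other school will carry on routine activity", and "The decision of selection of school for intervention therefore was based on convenience and was not randomized".

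Potential efficacy on physical activity, diet, BP, BMI and waist circumference is the second of the two aims at the end of the Background. The abstract's Conclusion makes wider replication depend on it: "If found feasible and demonstrating potential efficacy on physical activity, dietary behaviors, and cardiometabolic parameters". The closing Conclusion uses similar conditional wording.

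**The concern.** The planned tests do not match the stated design, in two separate ways.

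- **Class clustering.** Children in a class share a teacher, a timetable and the group sessions. Their changes over 10 months are likely to be correlated, and the Student t and chi-square tests assume that they are not. This can be corrected, because the class of each child is known.
- **Arm equals school.** With one school per arm, anything else that differs between the two schools over the 10 months is inseparable from SHEPP. Using change scores removes a stable baseline gap but not a different trend. A small p-value would show that the two schools changed differently, not that SHEPP caused the difference.

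What is at stake is the second aim and the decision attached to it. An apparent effect on activity, diet or cardiometabolic measures could be offered as support for replication when the test behind it does not have its nominal error rate.

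**Working it through.** **Inputs from the article.** 12 classes per school, 24 in all; 40 to 45 children per class; about 540 planned per arm (Sample size). 982 children recruited, 505 and 477 (Recruitment). One school per arm (Assignment of interventions).

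**Assumptions.** The article gives no ICC, so a range is shown. It states no significance level; two-sided 5% is used by convention. Normal approximation throughout. Loss to follow-up is ignored.

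**The plan's own figure.** 12 × 45 = 540 per arm reproduces, at the upper end of the class size (12 × 40 = 480 at the lower end). No design effect was applied.

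**Step 1: classes only.** Mean class size m = 982/24 = 40.9. Design effect DE = 1 + (m − 1) × ICC. The true standard error is √DE times the naive one, and the true error of a nominal 5% test is 2 × [1 − Φ(1.96/√DE)]. Effective n per arm is 491/DE.

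| Assumed class ICC | DE | SE multiplier | True error | Effective n per arm (of 491) |
|---|---|---|---|---|
| 0.01 | 1.40 | 1.18 | 9.8% | 351 |
| 0.02 | 1.80 | 1.34 | 14.4% | 273 |
| 0.05 | 3.00 | 1.73 | 25.7% | 164 |
| 0.10 | 4.99 | 2.23 | 38.0% | 98 |

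A simulation of 20,000 null trials per setting, with 12 classes of 41 per arm and a t test, agrees: 5.1% at ICC 0 (a check), then 9.7%, 14.2%, 26.3% and 38.1%. The simulation covers the t test only. The same design effect applies approximately to a difference in proportions, with the ICC taken on the binary scale, so the chi-square test errs in the same direction.

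**Step 2: adding school variance.** With total variance 1, school ICC s and class ICC c, the variance of the difference between arms is

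2s + 2c/12 + (1 − s − c)(1/505 + 1/477),

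against a naive 1/505 + 1/477 = 0.00408.

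- s = 0.01, c = 0.02: 0.02000 + 0.00333 + 0.00395 = 0.02729 (unrounded terms). Ratio 6.69, SE multiplier 2.59, true error about 45%.
- s = 0.01, c = 0.05: 0.02000 + 0.00833 + 0.00383 = 0.03217 (unrounded terms). Ratio 7.89, SE multiplier 2.81, true error about 49%.
- s = 0.001, c = 0.02: 0.00200 + 0.00333 + 0.00399 = 0.00932. Ratio 2.29, SE multiplier 1.51, true error about 20%.

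Simulation gave 45.1% and 48.5% for the first two settings.

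**Step 3: what can be estimated.** Between classes there are 24 − 2 = 22 degrees of freedom, so the class part can be estimated and corrected. Between schools within arm there are 2 − 2 = 0, so the school part can be neither estimated nor corrected from these data.

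**The case against.** The strongest reply is that this is a feasibility trial. Under Measures of feasibility, success is judged only on recruitment, retention and treatment fidelity above 70%, and these are reported as percentages. The faulty tests do not touch them. Under Study setting, feasibility findings are said to inform whether efficacy should be tested in future, so the trial is not presented as confirmatory. All of this stands and limits the point to the secondary outcomes. It does not remove the point, because potential efficacy is a stated aim and both conclusions tie replication to it.

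A second reply is disclosure. Limitations concedes the lack of randomization, selection bias and reduced internal validity. That covers part of the school problem. It mentions neither clustering nor the confounding of arm with school, and it changes neither the tests nor the conclusions. Randomizing these two schools would still leave one cluster per arm.

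Third, the ICCs are assumed, and they apply to change from baseline. Both schools belong to one education service and share curriculum and extracurricular design (Recruitment), so a small school variance is plausible, though not shown. The size is therefore open; the direction is not.

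Three stronger readings are tempting and are not supported. A reader might infer that the tests make a finding of efficacy likely even if SHEPP does nothing. Class clustering alone gives 10% to 38% per outcome over the range shown, and rates near one half need an assumed school ICC of about 0.01. The article also states no significance level and no rule equating potential efficacy with a significant test. A reader might say that the planned confidence intervals are too narrow, but no between-arm interval is planned; the direct fault lies in standard errors and p-values. And a reader might conclude that the feasibility verdict is compromised, which it is not.

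**Conclusion.** The point holds for the secondary outcomes. The article fixes its between-arm tests, and those tests contradict its own description of delivery and allocation. This is a method stated wrongly, not a detail left to an unseen analysis plan. A nominal 5% test has a true error of about 10% to 38% for assumed class ICCs of 0.01 to 0.10. It reaches about 45% to 49% if a school ICC of 0.01 is added to a class ICC of 0.02 to 0.05, and less if school variance is smaller. These figures rest on assumed ICCs and a conventional 5% level. Two conclusions need no particular value: the standard errors are too small for any positive ICC, and with one school per arm no analysis can attribute the difference to SHEPP rather than to the school.

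**What to change.** 1. **Statistical analysis, quantitative outcomes.** Replace the t test with a linear mixed model with a random class effect, or with an analysis of class means (12 v 12 classes, 22 df).
2. **Statistical analysis, categorical outcomes.** A linear mixed model does not replace the chi-square test. Use class-level proportions, or GEE or mixed logistic regression with a small-sample correction.
3. **Reporting.** Give estimates with 95% CIs. State that the intervals exclude between-school variance and that the contrast is a difference between two schools. Do not use p-values as evidence of efficacy. Add clustering and the one-school-per-arm confounding to Limitations.
4. **Both conclusions (abstract and closing).** Reword so that progression rests on the feasibility criteria, with effect estimates and class ICCs used to plan a cluster-randomised trial.

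The first two changes correct the class part only. The school part can be handled only by the wording in items 3 and 4, short of adding schools. No new children, schools or measurements are needed. The cost is wider intervals and a more modest statement about efficacy.

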## Methods

### Study setting

It is a parallel-group feasibility intervention trial. The justification for a feasibility design is that this is the first study to incorporate health education, physical activity intervention in children involving parents, teachers, and children. Secondly, feasibility studies are relied on to produce a set of findings that help determine whether an intervention should be recommended for future efficacy testing or not [26]. This feasibility intervention design to test SHEPP is therefore justified. It is being conducted in two schools located in lower to middle-income class, at different locations but having the same school curriculum under the Aga Khan Education Service, Pakistan (AKESP). Each school has approximately 2000 students, both boys and girls. Each school comprises of 10 levels of classes with 3-4 sections each. These 10 levels of classes are similar to the Cambridge O Level (but the curriculum is locally adapted), where level of education increases with each increasing class from 1 to 10. Sections refer to groups of children sitting in separate rooms but at the same level of education. The study is expected to complete in 18 to 20 months. The study flow is shown in Fig. 1. All children aged 9-11 years enrolled from the abovementioned schools were included. The rationale for this age limit is that in this period of 9-11 years age, physical activity starts to decline mainly in girls [27]. Those suffering from any physical disability were excluded from this feasibility study. If found feasible, specific physical activity for disable children by using additional aids might be useful in future studies. These children however will attend the health education teaching sessions according to the principles of ethical justice.

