### Limitations

The limitation of this study is the lack of randomization, including a select group of schools. This might result in selection bias, thus limiting the internal validity of the study. Secondly, the objective measurement of physical activity through an electronic wrist band is done only for 5% of the population; however, using this on the entire population would not have been cost-effective. We have not used direct objective measures to test the knowledge of children before and after the intervention; however, we will measure indirectly the change in behavior by looking at their physical activity and dietary behaviors. Also, testing them on knowledge in addition to regular schoolwork might have reduced their interest in SHEPP. Another important limitation is that we could not convince the school authorities to incorporate the physical activity sessions 4 times a week due to lack of time slots during school time. However, we will try to compensate for this by introducing between class activity and physical activity in assembly. The Pax good behavior game will be implemented in a basic format and might not be implemented in an ideal setting due to lack of training resources.

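### Change is compared between two non-randomised schools by an unadjusted t test, which leaves age and sex uncontrolled although both are already known

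*Protocol article*

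**What the plan says.** The Statistical analysis section of the protocol article fixes the test for the continuous secondary outcomes: a Student t test between the groups on "change in physical activity, BP, BMI, and waist circumference before and after intervention". Diet gets a chi-square test. No covariate is named for either. The intention-to-treat rule says that "all participants will be analyzed in the same group as at time of allocation", which settles group membership but not comparability of the groups.

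On allocation, Assignment of interventions states: "The decision of selection of school for intervention therefore was based on convenience and was not randomized". There is one school per arm, and the choice followed baseline: "One school is allocated to SHEPP intervention after baseline data collection". The Limitations section concedes the consequence, "This might result in selection bias, thus limiting the internal validity of the study", but no section gives an analytic response.

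The Study setting section explains the age range by saying that at these ages "physical activity starts to decline mainly in girls". The Recruitment section gives the numbers per school and the number of boys overall, but no age or sex distribution by school.

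**The concern.** A t test on change is unbiased only if the two schools would have changed by the same amount without SHEPP. Randomisation would make that credible on average; here nothing does. The article's reason for choosing this age range implies that age and sex predict change in activity. Growth over ten months makes the same plausible for BMI, waist circumference and blood pressure. If one school has more girls or older children, part of the difference in change reflects the mix of children and not the programme.

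The two Conclusion sections make wider roll-out depend on feasibility and on signs of benefit. The between-school estimates therefore feed a decision, although they are secondary. Age, sex and class are known from recruitment, so the named test leaves out information already in hand.

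**Working it through.** **Inputs from the article.** Recruited: 505 + 477 = 982. Boys: 496/982 = 50.5%, which matches the stated figure; it is not split by school. The article gives no effect size, SD, baseline to follow-up correlation or baseline gap for these outcomes, so there is no planned figure to reproduce. Everything below the standard-error line rests on assumed inputs.

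**Standard error.** In SD units, with children treated as independent as the t test does, sqrt(1/505 + 1/477) = 0.064. With this many children a small bias can reach significance.

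**Age and sex.** Bias = (difference in mean change per unit of covariate, in SDs of change) x (imbalance between schools). The unit is girls versus boys, or one year of age. With no true effect and a two-sided 5% test:

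| Effect on change | Imbalance | Bias (SD) | False-positive rate |
|---|---|---|---|
| 0.1 | 0.1 | 0.01 | 5.3% |
| 0.1 | 0.3 | 0.03 | 7.6% |
| 0.2 | 0.2 | 0.04 | 9.6% |
| 0.2 | 0.3 | 0.06 | 15.6% |

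For the last row, 0.06/0.064 = 0.94 standard errors. The consequence runs from negligible to material, depending on an imbalance that the article does not report.

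**Baseline value.** Let d be the baseline gap between schools in outcome SDs and r the baseline to follow-up correlation, with equal SDs. The SD of change is sqrt(2(1-r)).

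- *Transient gap* (follow-up depends on the observed baseline with slope r). The change-score contrast is biased by -(1-r)d. For d = 0.2 at r = 0.3, 0.5, 0.7 and 0.9, the size is 0.14, 0.10, 0.06 and 0.02 SD, and the false-positive rates are 46%, 35%, 23% and 11%. The baseline-adjusted model is unbiased.
- *Stable gap* (a lasting difference between the schools). The gap cancels in the change score, so its bias is 0. The baseline-adjusted model is biased by d - rd = (1-r)d.

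A simulation with 505 and 477 children, d = 0.3, r = 0.5, no true effect and 2000 runs agrees, with (1-r)d = 0.5 x 0.3 = 0.15:

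| Gap | t test on change | Baseline-adjusted model |
|---|---|---|
| Transient | bias -0.15 SD, 64% false positives | bias 0.00, 5.7% |
| Stable | bias 0.00, 5.4% | bias +0.15 SD, 77% |

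Each model fails where the other works, and the article does not say which kind of gap to expect.

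**The case against.** **Change already removes baseline.** A reader might infer that baseline differences between the schools pass straight into the effect estimates. The article does not support that. The tested variable is change, so each child's baseline is subtracted. Under the model above only a transient gap leaks, by the share 1-r, and a stable gap leaks nothing. Allocation followed baseline data collection, but the stated reason is convenience, and nothing suggests that the school was chosen on its baseline values.

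**A figure in minutes per day.** It is tempting to put the bias in activity units. No SD, correlation or school-level baseline is given to do so. With about 490 children per school, independent recall error largely averages out. A large gap between intact schools would more plausibly be a lasting difference.

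**Adjusting for baseline may do harm.** This stands. Making the baseline-adjusted model the sole main analysis would swap one unverifiable assumption for another.

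**No imbalance is shown.** Both schools are mixed, share a curriculum and supply the same age band, in general from classes 2 and 3. That limits the age difference but not the sex mix, and it does not balance age within the band. The size stays unknown.

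**Status.** The outcomes are secondary in a feasibility trial, the feasibility criterion is the 70% threshold, and the selection bias is admitted. This lowers the stakes. Admitting a bias does not reduce the part that recorded covariates could address. An unseen analysis plan may add adjusted models, but the article itself commits to the unadjusted test.

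**Conclusion.** The point holds for measured predictors of change. The article commits to an unadjusted t test on change between two schools chosen without randomisation. It thereby leaves age and sex uncontrolled, although its own rationale implies that they matter for activity and both are already known.

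The size cannot be stated. Over the assumed range shown, the age or sex bias runs from 0.01 to 0.06 SD and the false-positive rate from 5.3% to 15.6%. These rates treat children as independent. The baseline calculations do not show that the planned change score is wrong; they show that neither treatment of baseline can be taken as correct here.

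A reader might also infer that adjustment would make the comparison causal. It would not. With one school per arm, every school-level difference is fully confounded with SHEPP, and no covariate model removes it. The calculations cover the continuous outcomes, not the chi-square test for diet.

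**What to change.** For physical activity, BP, BMI and waist circumference:

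1. Replace the t test with a regression of change on arm, age, sex and class level.
2. Report beside it a model of the follow-up value on the same terms plus the baseline value. State in advance that neither is presumed correct, and report any disagreement between them as uncertainty about the effect.
3. Tabulate baseline characteristics, including age, sex and baseline outcomes, by school.
4. Describe the estimates as descriptive, because school and intervention cannot be separated.

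The cost is a little analysis time and one table. Baseline outcomes are already collected, and age, sex and class are known from recruitment, so no new data are needed. Confounding at school level remains and should stay among the stated limitations.

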## Outcome measures

### Measures of feasibility

Feasibility of SHEPP in terms of recruitment, retention, and treatment fidelity will be assessed. *Recruitment* is defined as the percentage of participants enrolled out of the total participants who were invited at baseline. *Retention* is defined as the percentage of participants who will be available for follow-up at 10 months out of those recruited at baseline. *Treatment fidelity* will be defined as the proportion of planned physical activity sessions held [33]. The trial will be considered as feasible if recruitment, retention, and treatment fidelity are > 70% recruitment [34].

Measure of potential effect

Physical activity levels (in school, out of school, moderate to vigorous physical activity, and sedentary time) assessed by change in time (minutes) spent in physical activity. Dietary patterns in terms of percentage increase in fruits and vegetable serving/day, and percentage decrease in sweetened beverages and snacks/day, cardiometabolic risk factors by change in BP, BMI, and waist circumference (WC).

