## Recruitment

We aimed to recruit children from schools working under the AKESP, primarily because, all these schools have the same design of curriculum and extracurricular activities. There are 3 schools working under the AKESP and based on logistics, we decided to conduct SHEPP in 2 schools within 10-km distance from the study center. Approval was taken from the head of schools in AKESP. After these principals of both schools were approached and at least 2 detailed meetings were held to discuss the designing of the study and recruitment. List of children aged 9-11 years studying in the morning shift (in general class 2 and 3) were obtained from the principals, and 1280 students were assessed for eligibility. After this informed consent and assent forms were distributed in each class by the PI and research staff of both schools. A note was also written in their dairies so parents could understand about SHEPP. One-week time was given to parents to agree or disagree to consent. Parents were given contact numbers of PI in case they have any queries. The consent forms and assent forms were distributed to 1191 eligible parents and their children, out of which 1116 (93.7%) agreed to participate. In all, the total number of children recruited were 982 (82.5 %); 505 from school A and 477 from school B. Out of them, 496 (50.5) were boys. To improve recruitment and to maintain interest of the participants posters will be developed which will be posted in each class and in the corridors.

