## Data collection, management, and analysis

### Data collection

Data collection will be done by trained data collectors who will be trained by the primary investigator for (a) filling data collection forms, (b) measurement of blood pressure, waist circumference, height, and weight. Assessment of outcomes will be done at baseline and then after 10 months of intervention by the data collectors. Physical activity would be assessed using the validated youth physical activity questionnaire modified for children at baseline and follow-up [36]. Based on the findings of a previous pretesting and piloting study (unpublished), netball, rugby, skiing, snowboarding, sledging, skateboarding, and walk-the-dogs were excluded, as these are very uncommon activities and sports in our settings. However, some common traditional games such as Kabaddi (wrestling), Pahel dooj (hopscotch), Kho kho (game of chase), Pithu garam (dodge ball), kittening, bay blades, marbles, and activities related to ascending stairs were included. In addition, religious activities like performing prayer, recitation of Quran—the holy book, and household chores like sweeping, moping, cooking, dishwashing, and grocery purchase were incorporated. Finally, the modified version consists of 71 different activities in the same seven domains of the original YPAQ form. Physical activity will also be measured objectively using Mi wrist bands for at least 5% (*n* = 50) of the participants, to check the validity of physical activity measured by the questionnaire. Mi wrist band has shown 96% accuracy of measuring physical activity when compared to the gold standard [37]. Dietary assessment will be done using a 24-h dietary recall. Number of raw fruit and vegetables, number of sugar-sweetened beverages and snacks/day that are eaten will be recorded at baseline and follow-up. The dietary recalls will be conducted by trained staff on non-consecutive day. Blood pressure will be recorded using Omron m5 monitors using a pediatric cuff [38].. Weight would be recorded using Tanita’s digital weight scales. Community-setting aluminum scale was used to measure height with subjects standing barefooted (without head cover).

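### The diet outcomes are defined as a percentage change in servings per day but assigned a chi-square test with no category defined, so the stated outcome and test do not fit

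*Protocol article*

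**What the plan says.** Three places in the protocol article bear on this point.

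- **Outcome measures, measure of potential effect:** "Dietary patterns in terms of percentage increase in fruits and vegetable serving/day, and percentage decrease in sweetened beverages and snacks/day". No formula, category or threshold follows.
- **Data collection:** "Dietary assessment will be done using a 24-h dietary recall", and "Number of raw fruit and vegetables, number of sugar-sweetened beverages and snacks/day that are eaten will be recorded at baseline and follow-up". The raw data are therefore counts at two time points.
- **Statistical analysis:** "Chi-square test to compare qualitative variables like percent increase in fruits and vegetables between the 2 groups from baseline to follow-up". The preceding sentence deals with the other outcomes: "Student *t* test would be used to compare quantitative variables (change in physical activity, BP, BMI, and waist circumference before and after intervention) between groups". Diet is not in that list.

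The Statistical analysis section also commits to including everyone: "Analysis would be done on intention to treat basis, that is, all participants will be analyzed in the same group as at time of allocation". The article does not say how a baseline count of zero would be handled.

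**The concern.** The outcome and its test belong to different types of data. A percentage change in servings is a number, and a Pearson chi-square test compares counts of children across categories. As written, the test cannot be applied to the outcome until someone supplies a categorisation that the article does not contain.

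The outcome has a second weakness if it is computed child by child. It divides by the baseline count, so it does not exist when that count is zero. Where the count is small it is unstable: a change from 1 to 2 is +100%, while the same one-serving change from 4 to 5 is +25%.

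What is at stake is the diet result, a secondary outcome and part of the second study aim. The Conclusion names dietary behaviour among the potential effects that would support larger-scale replication. With the definition open to several readings, the analysis could also be settled after the data are seen.

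**Working it through.** The article gives no sample size, power or expected value for the diet outcomes, so there is no figure to reproduce. The check is on definition and test, followed by an illustration of scale.

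**Step 1. Three readings of the outcome, set against the test.**

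| Reading | Fits the Outcome measures wording? | Zero baseline a problem? | Chi-square applies? |
|---|---|---|---|
| Percentage change in each child's servings | Yes | Yes | No |
| Percentage change in a group's mean servings | Possibly | Largely not | No |
| Percentage of children whose intake rose (or fell) | No; no responder is defined | No; 0 to 1 is an increase | Yes |

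No reading satisfies both sections as they stand.

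**Step 2. Where the child-level value is missing.** Percentage change = 100 × (follow-up − baseline) / baseline, which is undefined at baseline = 0. The documents give no servings data, so the share of zeros has to be assumed. For Poisson counts with mean m on one recall day, P(0) = exp(−m). If a child's recalls covered two independent days, P(0) = exp(−2m). For a more dispersed count (negative binomial with dispersion parameter k = 1, one day), P(0) = 1/(1 + m). The number recruited is 982 ("the total number of children recruited were 982 (82.5 %); 505 from school A and 477 from school B").

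| Assumed mean servings/day | Poisson, one day | Poisson, two days | Negative binomial, one day |
|---|---|---|---|
| 0.5 | 0.607 (596 of 982) | 0.368 (361) | 0.667 (655) |
| 1 | 0.368 (361) | 0.135 (133) | 0.500 (491) |
| 2 | 0.135 (133) | 0.018 (18) | 0.333 (327) |
| 3 | 0.050 (49) | 0.002 (2) | 0.250 (246) |

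The counts use all recruited children. The number with follow-up will be smaller.

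**Step 3. What the percentage scale does to the remaining children.** Take independent Poisson counts with the same mean m at both visits, so that nothing truly changes. Among children with baseline B > 0, the expected percentage change is 100 × (m × E[1/B | B > 0] − 1).

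- m = 0.5: 100 × (0.5 × 0.879 − 1) = −56%
- m = 1: 100 × (1 × 0.767 − 1) = −23%
- m = 2: 100 × (2 × 0.577 − 1) = +15%
- m = 3: 100 × (3 × 0.433 − 1) = +30%

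The mean absolute change over all children is zero in every case. So the scale would lose children and also shift the average within each arm.

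**Step 4. What a rise/no-rise split costs.** In a simulation with 505 and 477 independent Poisson children, no clustering and a true gain of 0.2 servings/day in one arm, chi-square on any increase was compared with a t test on change in servings. Power was 84% against 84% at a baseline mean of 0.5, 49% against 61% at 1, and 25% against 33% at 2. The loss is not universal, but it appears once intake is not very low.

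**The case against.** The strongest reply is that the Statistical analysis section has its own logic. Quantitative variables get means and a t test, categorical ones get frequencies and chi-square, and the diet item is placed with the second group. On that logic the authors probably meant the percentage of children whose intake increased. Chi-square is then valid and zero baselines do no harm. A responder cut-off is also the kind of detail that a condensed article may leave to a fuller document. This stands as a plausible reading. It does not dispose of the point, because the Outcome measures section describes a percentage change in servings per day. The article states both an outcome and a test, and the two disagree.

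A reader might infer that the plan excludes children who eat no fruit or vegetables. The article does not say so. It commits to analysing all participants, and exclusion would follow only from the child-level reading. Nor does the text support calling such children the main target of the teaching, since every enrolled child is taught and diet is one of six sessions. Diet is not singled out as a key secondary outcome either; it is one of several.

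The illustrated shares are also open to challenge. Both the distribution and the means are assumed. Data collection refers to dietary recalls in the plural on a non-consecutive day, which may mean more than one day per child and therefore fewer zeros.

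Finally, a binary outcome is less informative but not an error, so a count model is an improvement and not the only way to resolve the contradiction.

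**Conclusion.** The point holds as a mismatch between the stated diet outcome and the stated test. A child-level percentage change is numerical, is undefined at a zero baseline and cannot be compared by chi-square. The reading under which chi-square works is not the one in the outcome definition, and it gives up the size of change.

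The share of children without a value is unknown. For one recall day it is about 61%, 37%, 14% and 5% at assumed means of 0.5, 1, 2 and 3 servings/day under Poisson counts. It is higher with more dispersion and lower with more recall days. These figures show that the problem could be anything from minor to dominant; they are not an estimate for this trial.

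The consequence is confined to a secondary outcome of a non-randomised feasibility trial. Recruitment, retention and treatment fidelity, and the feasibility criterion built on them, are not touched.

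**What to change.** **Preferred.** Define each diet outcome (fruit and vegetables, sweetened beverages, snacks) as servings/day at follow-up. Compare the schools with a model adjusted for baseline servings: a count model such as the negative binomial, reporting a ratio of means, or ANCOVA on servings, reporting a difference of means. Give the 95% CI. Enter class as a random effect; classes are nested within the two schools, so fixed class effects would absorb the school comparison. A ratio of means keeps a percentage interpretation, and either model includes children with a zero baseline.

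**Minimum.** If chi-square is kept, rewrite the outcome definition as a binary responder with a stated rule, applied in the same way to beverages and snacks, and state that children with a zero baseline are classified by that rule.

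**Cost.** A reworded secondary outcome and slightly more analysis work, on data already planned. Neither option removes the confounding that comes from having one school per arm, so the comparison remains descriptive of two schools.
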